## Abstract

**Background:**

The increasing number of requests for help for acutely ill patients and their management is a major problem in the health systems of many countries, but especially in Germany. Rescue coordination centers and ambulances in Germany are increasingly overloaded. As a result, rides as a part of rescue operations have been increasing in length for years, yet a relevant proportion of these operations represent low-acuity calls (LACs). The basic objective of this pilot study is the quantitative analysis of the potential misuse of requests to the rescue control center. Indications for alternative treatment options and how to handle these treatment options in nonacute, non–life-threatening health conditions, such as minor injuries or minor infectious diseases, will be assessed. The identification of these LACs is vital in order to prevent health care resources in emergency medical care becoming inadequate.

**Objective:**

The overarching goal of this study is to determine the percentage of unnecessary rescue missions on site and subsequently to obtain an impression of the paramedics’ assessment of alternative treatment options or alternative methods of rescue transportation.

**Methods:**

This will be an exploratory, noninterventional, cross-sectional study with a quantitative approach. The study is multicentric, with 21 ambulances in 12 different locations. The data for this study were collected via a questionnaire, newly developed for this study, for rescue personnel. Additionally, secondary data from the responsible control center will be linked and processed in an initial descriptive analysis. This descriptive analysis will form the basis for a subsequent variance analysis.

**Results:**

Data collection started as projected on September 18, 2023, and was ongoing until end of November 2023. We expect the documentation of several thousand rescue operations. We expect the following study results: (1) many unnecessary rescue operations, (2) immediate on-site assessment of correct care and treatment, and (3) patients’ reasons for calling a rescue coordination center.

**Conclusions:**

To our knowledge, this is the first observational study in which acute rescue operations are recorded on site. The focus of this study is on the trained paramedics’ assessment of whether rescue operations are necessary or not. Additionally, alternative treatments, such as out-of-hours care service or primary care service, are shown for each individual case. The study also intends to cover the question of which factors are relevant and statistically significantly connected to the misuse of ambulances.

**Trial Registration:**

German Register for Clinical Studies (Deutsches Register für Klinische Studien) DRKS00032510; https://drks.de/search/en/trial/DRKS00032510

**International Registered Report Identifier (IRRID):**

DERR1-10.2196/54002

## Introduction

The number of outpatient medical treatment cases in Germany has been showing an upward trend for years [1]. Additionally, the number of rescue operations in emergency medical service (EMS) shows a continuous annual increase of about 5%, amounting to almost 16.5 million emergency ambulance and emergency missions in the 2016-2017 observation period [2-5]. This increase can also be observed in the number of rescue operations performed by the ambulance service and is similar in most European countries, as well as in the United States and Australia [6-9]. The steady increase can only partly be accounted for by demographic developments or geographical peculiarities [10,11]. Rather, a not inconsiderable proportion of EMS operations and the resulting transports to an emergency department (ED) do not seem to be indicated from a medical point of view [12-14].

In Germany, patients with minor ailments should generally be treated in medical on-call service centers out of hours when their own general practitioner (GP) is not available. GPs and specialists are obliged to work in medical on-call services; in some regions this is only out of hours, while in other regions it is 24 hours, 7 days a week. The medical on-call services are regulated by the Association of Statutory Health Insurance Physicians, that is, they are self-administered. Everybody, whether seriously or only slightly ill, can consult the ED as well as clinics and the EMS. EDs are also responsible for, preferably, emergency care but also for all other acute patient concerns. [15]. In addition to a lack of professional assessment on the part of those seeking help and ignorance of the responsibilities of the existing emergency and acute patient care structures [16,17], a variety of factors can lead to the EMS and ambulance service being alerted in nonurgent cases. Apart from the possibility of low-threshold and timely care by the ambulance service, these also include the patient-specific perception of their urgency as well as a personal need for safety [18]. Other circumstances that occasionally lead to avoidable requests for ambulance service include nursing home patients with ambulatory care–sensitive conditions, older people with many comorbidities not receiving timely outpatient consultation appointments, and people with mental health problems or somatoform disorders requiring psychological care [19-25].

The increased and undifferentiated use of the EMS means rising costs at the expense of social insurance [26] and a higher workload for emergency medical staff, who are exposed to an extremely high risk of burnout [27,28]. This also leads to overcrowded EDs and therefore to great difficulties treating patients efficiently and at a high quality outside of regular and scheduled consultations [29,30]. Besides this, the response time of the EMS tends to be more and more extended, and statutory provisions consequently cannot be observed [31,32]. Serious doubts concerning the capability of the EMS and the emergency medical system in general are being seen more and more in public debate in recent years.

German policy makers are now seriously addressing this issue after making some local short-term changes; for example, alert keywords have been restricted for ambulances on call. Recently, a German government commission proposed comprehensive modifications to the EMS. These call for extending the EMS’s entitlement to services and fees for care and treatment of minor ailments on site, not just transportation (as before). The overall aim is to reorganize and expand the existing components of the EMS [33].

The aim of this prospective cross-sectional study is the quantitative analysis of unnecessary ambulance missions, in addition to the examination of indications for alternative care options in nonacute life-threatening situations instead of transport by the ambulance service to a hospital ED. Alternative health care options should be discussed to help improve care for acute patients and reduce the misuse of ambulances.

## Methods

### Aim

This study intends to quantify the fraction of low-acuity calls (LACs) in ambulance operations, focusing on alternative treatment options. For this purpose, the trial will evaluate how often EMS personnel rate a different, usually ambulatory treatment as being more suitable because a patient has a non–life-threatening health condition that does not require any urgent medical intervention. In addition, this study aims to identify and quantify the reasons why patients without a life-threatening medical condition or other medical indications are brought to an emergency room by ambulance instead of being transferred to a more suitable location for treatment. Therefore, the 2 main questions the study plans to cover are, first, what kind of treatment patients of the EMS need, if not emergency treatment and urgent conveyance to a hospital, and second, why patients may not receive adequate medical care. A quantitative approach is required to obtain an indication of the dimensions of these individual aspects, as there is usually no standardized documentation by the control center that goes beyond the point of “patient was taken to hospital/patient was referred to GP/refusal of transport/no patient was found,” which represents only part of the actual situation. Furthermore, the study will collect and analyze data on operational statistics to determine if conditions like operation time, day of the week, accessibility to a GP, priority, and content of the alert (as set by the dispatcher in the control center) have an impact on the frequency of LAC operations. We will also evaluate socioeconomic factors, such as age and gender of the patient, as well as the impact of the operation area.

### Design

The key feature of this exploratory, noninterventional, cross-sectional study is a web-based questionnaire (Table 1) for tablets or smartphones. In the first phase, each individual question on the web-based questionnaire was reviewed by an expert panel at the Department of General Medicine at Heidelberg University Hospital, and in the second phase, the questions were discussed with the heads of operations at the rescue coordination centers, as well as with selected paramedics. The focus was on the feasibility of this pilot study. When this study is rolled out (at large scale) there also will be analyses of interrater reliability.

**Table 1 table1:** Questionnaire for ambulance crews on emergency cases.

Item	Content
Operation number	(Free text)
Patient gender	Male Female Gender-diverse
Patient age group (years)	18-24 25-39 40-59 60-64 65-79 ≥80
Operation time on a weekend day or holiday^a^	Yes/no
Operation time during main opening hours of general practitioner care^b^	Yes/no
Classification of operation area (number of inhabitants)	Metropolitan (>100,000) Urban (30,000-100,000) Suburban (10,000-30,000) Rural (<10,000)
Working diagnosis	(Free text)
Treatment or procedure performed (multiple choices possible)	Being conveyed to a hospital Referral to a general practitioner or medical on-call service Continuance at home Patient refused being conveyed Therapeutic measures performed (Free text)
Appropriate treatment or procedure (multiple choices possible; no choice possible)	Being conveyed to a hospital autonomously Calling on the medical on-call service autonomously Consulting the general practitioner for further care Exclusively counseling Counseling by telephone possible Social caretakership Being conveyed by a patient transport ambulance (Free text)
Reasons for being conveyed to a hospital without medical indication (multiple choices possible; no choice possible)	Missed transportation opportunity by patient or relatives Patient insists on being conveyed by ambulance Social indication House call by general practitioner or medical on-call service indicated but not provided Medical on-call service not favored by patient Insecurity of team leader Language barrier (Free text)

^a^As defined by the state in which the operation took place.

^b^Main opening hours were defined as Monday, Tuesday, and Thursday from 7 AM to 7 PM, and Wednesday and Friday from 7 AM to 2 PM.

The members of the expert panel determined which crucial dimensions of medical emergency treatments will be queried, including (1) working diagnosis, which is the assessment made on site by the ambulance crew with consideration of diagnostics that can be carried out preclinically; (2) procedures, including the ambulance crew’s approach to counseling, treatment, patient transport, and referral to other caregivers; (3) adequacy of care, that is, the assessment of the most suitable form of care, which is carried out by the ambulance crew based on the situation on site; and (4) problems that arise, that is, the evaluation of possible reasons why patients are not directed to the form of care that has been assessed as being most suitable.

The training of the paramedics consists of 5 vital elements. The important questions for assessing their concerns about possible rescue operations (Textbox 1) are described in in-person lectures. The five *W* questions are integrated in the questionnaire and special training is provided.

*W* questions and example cases.

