### Data Analysis

The two main outcomes for our analyses are the number and percentage of inappropriate emergency calls and the reasons for patients being conveyed to a hospital without a medical indication. This total numbers will be further subdivided according to the paramedics’ assessments. Moreover, it is of interest if there are explanatory variables such as patient gender, patient age, operation area, and operation time in the data set that might be associated with inappropriate emergency calls or being conveyed to a hospital without a medical indication. This will be analyzed based on multivariable regression modeling [35]. To calculate frequencies, rates, and percentages, we will use the PROC SQL procedure in SAS (version 9.4, SAS Institute). To perform the multivariable analyses, we will use the PROC GENMOD procedure in SAS. For qualitative analyses, we will use MAXQDA (version 24.1, VERBI Software).

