## Discussion

To the best of our knowledge, this is the first observational study in which acute rescue operations are being recorded on site in Germany. This study was initiated to show how many inappropriate rescue operations, such as those for minor injuries or minor infections, take place in a defined study period. The assessment of these LACs is carried out directly on site by trained rescue personnel and not later in the clinic. The assessment is therefore supplementary and can provide information on operations without the need for a referral, which is a main strength of this study. Another focus is on a preclinical assessment to determine suitable, diverse alternatives to transport by ambulance to an ED for patient conditions that do not require urgent treatment.

One major intent of our study is to complement previous work, which includes several retrospective clinical evaluations and many qualitative studies, such as interview studies, on reasons for calling the EMS in LAC situations as seen through the eyes of patients, as well as of caregivers (mostly EMS personnel), and what circumstances encourage these calls [36-38]. It is known from previous data that around 30% to 35% of all rescue service operations transporting patients to the ED are rated as inadequate and unnecessary [5-8], so a similar proportion of operations with preferred alternative care methods is expected. Most of these inadequate EMS operations involve patients whose health conditions are assessed as being able to be adequately treated by a GP or in general outpatient care [6], which is why there may be a significant difference in the number of primary care–sensitive EMS operations depending on the general availability of and access to general practices and medical out-of-hours care [17]. Additionally, we anticipate that a certain number of transportation operations by ambulance for LACs will take place because of missing transportation alternatives, which has been found to be a relevant reason for ambulance misuse in previous work [39,40]. Previous studies have shown differences in the use of emergency services between urban and rural populations [41], as well as between groups with differences in relevant socioeconomic factors, such as age and personal mobility [42], which may be confirmed in this study.

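### The reasons item counts failed outpatient access only as a missing house call; other access failures go to free text that the plan does not say will be counted, so the ticked access share is likely understated

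*Protocol article*

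**What the plan says.** The Data Analysis section names two main outcomes, and the second is "the reasons for patients being conveyed to a hospital without a medical indication". The Aim section says these reasons are to be quantified.

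The instrument is the last item of Table 1 (Design): "Reasons for being conveyed to a hospital without medical indication (multiple choices possible; no choice possible". Its seven fixed options are lack of transport, patient insistence, social grounds, a house call that did not take place, dislike of the on-call service, uncertainty of the team leader, and language. A free-text field follows.

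- The one option on outpatient supply is "House call by general practitioner or medical on-call service indicated but not provided".
- Two options record what the patient wants: "Patient insists on being conveyed by ambulance", and the first entry in "Medical on-call service not favored by patient Insecurity of team leader Language barrier (Free text".

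The Design section also says that this part of the form should explain why patients did not reach the care that the crew judged most suitable. The preceding item of Table 1 lists seeing the GP and going to the on-call service among the suitable alternatives.

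Elsewhere the article treats access as a cause. The Introduction lists older patients "not receiving timely outpatient consultation appointments" among the sources of avoidable requests. The Aim section lists GP accessibility as a condition to be analysed. The Discussion expects the number of primary care–sensitive operations to differ "depending on the general availability of and access to general practices and medical out-of-hours care".

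**The concern.** The form lets a crew record that a GP or an on-call practice would have been the right place. It gives no fixed option for saying that this place was closed, could not be reached or had no appointment. For a patient able to travel, the house-call option does not fit.

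A main outcome meant to be quantified then has a category that is only partly countable. The article says its results may inform interventions and political change in urgent care. A table of ticked reasons would show access failure as rarer than the crews saw it, and nothing in the table would tell the reader so. The limitations in the Discussion cover differing assessment standards, selective capture and recall, but not this gap.

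**Working it through.** The article gives no figure for the frequency of any reason, so there is nothing to reproduce. The check compares the form with the plan's own statements, followed by an illustration with assumed shares.

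**Step 1. Suitable care against recordable reasons (Table 1).**

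| Care judged suitable | Why it was not reached | Fixed option? |
|---|---|---|
| House call by GP or on-call service | Not provided | Yes |
| GP practice | Closed, unreachable or no timely appointment | No, free text only |
| On-call practice | Closed or unreachable | No, free text only |
| On-call practice | Patient does not want it | Yes |

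**Step 2. What happens to free text.** The Data Management section sends it to a separate qualitative analysis, whose stated purpose is to understand patients' motives. The Data Analysis section names software for frequencies and percentages and different software for the qualitative part. Neither section says that free-text reasons will be coded into the counted categories.

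**Step 3. Size, with assumed inputs.** Suppose A = 20 of 100 non-indicated conveyances are due to access failure. Let h be the share of these entered under the house-call option.

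- Ticked access count = A × h. Shortfall = A × (1 − h).
- h = 0.25: ticked 5, shortfall 15.
- h = 0.50: ticked 10, shortfall 10.
- h = 0.75: ticked 15, shortfall 5.

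The shortfall is above zero whenever h is below 1.

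**Step 4. Preference options.** Let m be the share of missed cases that crews tick as a preference that was not in fact the reason. Excess preference ticks = A × (1 − h) × m. At h = 0.50:

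- m = 0: excess 0.
- m = 0.5: excess 5.
- m = 1: excess 10.

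The documents give neither h nor m. The shortfall in Step 3 follows from the option list once some access failures are not entered as missing house calls. The excess in Step 4 needs a further assumption about crew behaviour.

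**The case against.** The strongest reply is that the reason can be recorded. The item ends in free text, and the fourth training case in the Design section shows a crew adding an unlisted, access-related reason (the patient had not heard of the on-call service). The questions were reviewed by an expert panel and discussed with heads of operations and paramedics, in an exploratory pilot focused on feasibility. Coding rules may also be left to a fuller document. This stands so far as it shows that the information is not lost. It does not settle how that information enters the counts, because the article describes a separate route for free text.

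The access passages also do not all concern this item. The Discussion's expectation is about how often such operations occur, which operation time and regression partly address. The Introduction's remark is about why people request an ambulance. They show that the article regards access as a cause, but not how often it leads to conveyance.

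Three stronger readings are tempting, and the documents do not support them.

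- **That patient preference is overstated.** Crews facing an unlisted reason may type it, tick something else or leave the item blank. Several options may be ticked, so a patient can insist and also face a closed practice, and both ticks are then true. The excess can be zero, and preference shares cannot be called upper bounds.
- **That access failure is invisible in most hours.** Table 1's footnote gives GP opening hours of 3 × 12 + 2 × 7 = 50 per week, which leaves 168 − 50 = 118 hours (70%). The form records for every operation whether it fell inside those hours, and the on-call service exists for times when the GP is unavailable. The 70% therefore measures neither access failure nor bias.
- **That an option on payment for on-site care is missing.** The Introduction reports a proposal on "fees for care and treatment of minor ailments on site, not just transportation (as before". This describes a system-level rule. Nothing in the article presents it as a reason a crew would give for an individual conveyance.

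**Conclusion.** The point holds in a limited form. The fixed options cover failed outpatient access only for house calls, and other access failures reach only free text that the article does not say will be counted. If the plan is followed as written, the ticked access share in the second main outcome is likely to be understated.

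The size is unknown. Under the assumed 20 access cases per 100 non-indicated conveyances, the shortfall is 15, 10 or 5 for a house-call capture of 25%, 50% or 75%. The direction rests on two assumptions: some access failures are not house-call failures, and crews seldom tick the house-call option when no access failure occurred. No direction can be given for the preference options.

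The gap can be largely repaired at analysis and does not invalidate the outcome.

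**What to change.** For the data already collected:

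1. Code free-text access reasons (practice closed, service unreachable, no timely appointment) into one category under a rule written before tabulation. Report it beside the ticked reasons, with ticked and coded counts shown separately.
2. Report how many reasons items were left blank among non-indicated conveyances, and state how those conveyances were identified.
3. Tabulate the reasons inside and outside GP opening hours, using the item already on the form.
4. State that the form had no fixed option for closed or unreachable practice care or for missing appointments, so the ticked access share is a lower bound. Make no corresponding claim about preference shares.

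For the roll-out, add one option to the reasons item: *GP or on-call practice closed, unreachable or no timely appointment*.

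The cost is a small amount of coding work, one stratified table, one sentence among the limitations, and a form one option longer. Coding cannot recover reasons that crews neither ticked nor typed, which is why the blank count belongs in the report.

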### Data Management

Data management is performed by the data management team of the Department of General Practice and Health Services Research of the University Hospital Heidelberg. The secondary data are collected by the control center of Ludwigshafen and are unrelated to the described questionnaire; they are governed by their own data management team.

Each data set is directly sent to and filed on a dedicated study server in the Department of General Practice and Health Services Research of the University Hospital Heidelberg. This also applies to the required secondary data transferred from the control center. Data access is granted only to the research staff directly involved in data collection and analysis. There will be no passing on of the unprocessed data to any external institution. Additionally, secondary data from the responsible control center will be linked and processed in the initial descriptive analysis. This descriptive analysis will form the basis for the variance analysis (see Data Analysis section). Working diagnoses will be converted to *International Classification of Diseases, Tenth Edition* codes by a research physician. The free-text entries will be analyzed separately with qualitative methods to obtain a deeper insight into patients’ motives for their behavior. Data storage and extraction will be performed with MySQL Community Server x64 (Oracle Corp).

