Several limitations of this study should be noted. The whole system of EMS and acute patient care is complex and includes many variables that cannot be examined in this study. For example, the control centers’ process for receiving emergency calls and dispatching ambulances plays a major role during all ambulance operations and the management of acute patients. Assessments of patients’ health condition by dispatchers, EMS personnel, and the patients themselves may greatly differ [43]. Misclassification can occur due to different assessment standards because there are usually no uniform classification criteria. There are approaches to harmonizing the triage and dispatching process, such as an intervention in out-of-hours care call centers in Germany that started in 2017 [44], but currently there exist no mandatory and coherent structures in emergency or rescue coordination centers.

In general, studies concerning the EMS in Germany deal with limited generalizability because of huge regional differences in standard operating procedures for treatment, equipment, staffing of rescue resources, and laws and regulations [45]. This is due to the federal structure in Germany and the accountability for civil protection lying mostly with the federal states or even autonomously with the local authorities [46].

Another limitation is the risk of bias. Operations that the ambulance crew rates as having been inappropriately dispatched are more likely to be captured than operations that fulfill the original functions of the EMS. Additionally, recall bias could occur if the questionnaire is not filled in soon after the end of an operation. Our intention was, in any case, to document all rescue operations regardless of urgency.

Nevertheless, the results of this cross-sectional pilot study may form the basis of further evaluations of possible interventions and pilot projects, the implementation of additional services in urgent care, support for change in the way patients are treated, and political change concerning urgent care in general.

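### The reasons item has no preset for dispatch or EMS organisation and its free text is not planned to be counted, so such reasons are likely under-recorded in the second main outcome

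*Protocol article*

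**What the plan says.** On ambulance transport to emergency rooms, the Aim section of the Protocol article states that "this study aims to identify and quantify the reasons why patients without a life-threatening medical condition or other medical indications are brought" there. Data Analysis makes "the reasons for patients being conveyed to a hospital without a medical indication" one of two main outcomes. Design describes the underlying dimension broadly, as "the evaluation of possible reasons why patients are not directed to the form of care that has been assessed as being most suitable", with no restriction to causes on the patient's side.

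The only stated source for this outcome is the last item of Table 1, the tenth in order (item 10 below). It has seven presets and an open field. Several choices are allowed, and so is none. The list ends with "Medical on-call service not favored by patient Insecurity of team leader Language barrier (Free text". The item before it (item 9) asks which care would have been appropriate, and its options end with "Social caretakership Being conveyed by a patient transport ambulance (Free text".

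On the open fields, Data Management says: "The free-text entries will be analyzed separately with qualitative methods". The purpose given there is insight into patients' motives. The Discussion says of the control centers that their "process for receiving emergency calls and dispatching ambulances plays a major role during all ambulance operations", and gives this as an example of system variables that the study cannot examine.

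**The concern.** A closed list largely decides what can appear in a frequency table. If a class of reasons has no box, and the open field is read separately for another purpose, that class is missing from the table even when crews know of it. A reader could then take its absence as evidence that it is rare.

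This matters because the reasons are to be quantified as a main outcome. The Discussion also expects the results to support further interventions and political change in urgent care. A table in which EMS organisation has no row is a weak basis for that, unless the gap is repaired or stated.

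**Working it through.** The plan gives no figure to reproduce. The check is a classification of the presets, a comparison of items 9 and 10, and share arithmetic on declared assumptions.

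**1. Presets of item 10, by where the reason lies**

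| Side | Presets | Number |
|---|---|---|
| Patient, social situation or communication | transport opportunity; patient insists; social indication; on-call service not favored; language | 5 |
| Outpatient service | house call indicated but not provided | 1 |
| Crew | insecurity of team leader | 1 |
| Dispatch or EMS organisation | none | 0 |
| Total | | 7 |

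**2. Item 9 against item 10.** A crew that conveys a patient and judges a patient transport ambulance suitable can record that judgement in item 9. Item 10 has no preset for why the emergency ambulance drove instead, for example because the other vehicle was not sent or not free. This is a practical alternative: Setting lists up to 28 such vehicles alongside 21 ambulances. In these cases the crew may also leave item 10 blank because the hospital visit itself was indicated and only the vehicle was not. A blank can therefore mean several things.

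**3. Other routes into the counts.**
- *Free text:* analysed separately and qualitatively. The article states no coding into the counted categories.
- *Linked control-center data* (Data Collection): alert time, priority, keywords and a feedback code. As described, these characterise the operation and do not give a reason for conveyance.
- *Blank:* allowed, and not distinguishable from an item that was skipped.

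**4. Effect on the patient-side share.** Let p be the true patient-side share of reasons and s the share that is dispatch or EMS organisation and has no preset. Take one reason per operation for simplicity. Assumed values, not from the documents: p = 0.60; s = 0.05, 0.15, 0.30.

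| Reading | Formula | s = 0.05 | s = 0.15 | s = 0.30 |
|---|---|---|---|---|
| Per eligible conveyance, no substitution | p | 60% | 60% | 60% |
| Ticked reasons as denominator | p/(1 − s) | 0.60/0.95 = 63% | 0.60/0.85 = 71% | 0.60/0.70 = 86% |
| Every such case ticked as patient-side | p + s | 65% | 75% | 90% |

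In all three rows the preset counts for dispatch and EMS organisation read 0%. The patient-side share moves only in the second and third rows. The third row is an extreme, because it needs every such case to be mis-ticked. The article fixes no denominator.

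**The case against.** A reader might infer that the item cannot count service-side causes at all. The document does not support that. The house-call preset is on the outpatient service side and team-leader insecurity is on the EMS side. The open field can also hold any unlisted reason. The fourth training case in Design shows a crew using it that way, and separate qualitative analysis does not rule out later coding. Such detail may stand in a full plan that is not shown.

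A reader might also infer that the distribution overstates patient behaviour by construction. That is not shown either. Nothing forces a patient-side tick, since several choices or none are allowed, and the share per eligible conveyance is unchanged without substitution. Several of the five presets describe circumstances rather than behaviour: Design explains social indication through immobility or lack of transport.

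A third tempting reading is that fee or mandate rules are a cause of conveyance established by the document. The Introduction only reports a reform proposal to extend the service's "entitlement to services and fees for care and treatment of minor ailments on site, not just transportation (as before"). It does not say that crews convey for that reason. Table 1 lists staying at home and referral among performed procedures, and the training cases show non-conveyance being offered and used.

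Finally, item 10 asks why the patient was conveyed, not why an ambulance was sent. Alert priority and content are analysed for their effect on the frequency of low-acuity calls, and the dispatch limitation is disclosed. The questions were also reviewed by an expert panel and discussed with heads of operations and paramedics.

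All of this stands, and it narrows the point. It does not close the gap between items 9 and 10. That gap is about conveyance, and the disclosed limitation does not link dispatch to the reasons outcome. A later analysis plan can code free text, but it cannot restore a tick box.

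**Conclusion.** The point holds in a limited form. Item 10 has no preset for dispatch or EMS-organisation reasons, most clearly for the non-use of a patient transport ambulance that item 9 allows as suitable. As the article describes the analysis, such reasons have no planned place in the counted second main outcome and are likely under-recorded.

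How many operations are affected cannot be derived from the documents. Any inflation of the patient-side share is conditional on the denominator or on substitution by crews, and the percentages above only illustrate assumed inputs. This is an inexpensive improvement to a main outcome and not an error that invalidates it.

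**What to change.** **For the forms already collected** (the Results section puts the end of collection at the end of November 2023):

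1. Before tabulating, code item 10 free text into prespecified service-side categories, including one for a patient transport ambulance that was suitable but not sent or not available. Count these together with the presets.
2. Report percentages per conveyed operation with an alternative ticked in item 9, and show a blank item 10 as its own row. Item 10 entries from operations without conveyance, as in the fourth training case, then fall outside this table and can be listed apart.
3. Tabulate separately the operations in which item 9 names a patient transport ambulance.
4. State that the distribution is not a full ranking of causes, and link the dispatch limitation in the Discussion to this outcome.

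**For the large-scale roll-out** mentioned in Design: add one preset for a patient transport ambulance suitable but not sent or not available, and one general preset for EMS organisation or service rules. Explain both in the briefing.

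**Cost:** a short coding step on text that is read anyway, two more tick boxes, and a line in the briefing. Coding cannot recover reasons that crews did not write down, so some under-recording will remain in the pilot data.
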